#### Range of motion measurement

To determine the range of motion (ROM), an isokinetic dynamometer (Genu3 Easytech, Florence, Italy) will be used. Participants will be seated with a hip joint angle of 110°, and their knee will fully extend on the dynamometer. Moreover, participants will be secured with a strap on the upper body to exclude any evasive movement. The foot will be fixed with a strap to the footplate of the dynamometer. Moreover, the upper leg will be fixed with a strap to avoid any movement of the knee. Participants will first move to the neutral knee joint position in the dynamometer (90°). They will then regulate the motor of the dynamometer to get into dorsiflexion (stretching) position until the point of discomfort is reached.

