### Outcomes {12}

#### Primary outcome: muscle architecture, tendon length, tendon thickness, muscle power, torque, and work

Muscle CSA, FL, MT, and PA will be examined with ultrasound imaging (Esaote, Technos MPX) in B-mode with a 10-MHz linear array transducer. This technique uses sound waves at fixed frequencies to create real-time images of the limb musculature in vivo (Esaote, Technos MPX, ultrasound). Conventional B-mode ultrasound can provide both quantitative and qualitative information on skeletal muscle tendons and ligaments [50]. Muscle ultrasound is a reliable method for the measurement of human FL, PA [33], and MT in B-mode images [46]. Also, ultrasound is a reliable and valid tool for the assessment of muscle size in older adults, ICC scores ranging from 0.92 to 0.999 [11].

Each of muscle power, torque, and work will be measured using isokinetic dynamometer test. An isokinetic dynamometer (Genu3 Easytech, Florence, Italy) will be used to estimate knee range of motion (ROM), passive resistive torque, power, and work for thigh muscles in an angular speed of 90° per second. Test-retest reliability will take place 2 weeks before the intervention (the same test twice over a period of time to a group of individuals). The scores from time 1 and time 2 can then be correlated in order to evaluate the test for stability over time. The Pearson product-moment correlation coefficient will be used to measure the strength of the linear relationship between the variables. Three to four submaximal practice trials will be given before each of the assessments. Knee extensor and flexor muscle power and work will be measured as the peak torque obtained over 3 trials during an isokinetic contraction using the passive concentric mode to test throughout the entire range of motion. Passive resistive torque will be obtained over 3 repetitions at the same speed degree. Peak torque will be gravity corrected using the Genu3 Easytech software.

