#### Passive resistive torque

Participants will be positioned with their hips at approximately 80° (to minimize hamstring stiffness) and their knees at a maximal extension. Stabilization straps are placed over the knee, foot, and ankle. The knee moves passively through six continuous cycles between 10° plantar flexion and 10° dorsiflexion at 90°/s, with neutral (0°) being the line of the tibia perpendicular to the footplate. The participants will be instructed to do the maximum plantar and dorsiflexion. Visual analysis of the curves will demonstrate consistent torque profiles, which indicate passive resistive torque.

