#### Isokinetic muscular power and work test

The power of knee extensor and flexor muscles will be measured in a sitting position using isokinetic dynamometers (Genu3 Easytech, Florence, Italy). After warm-up exercises, patients perform 4 maximal concentric strokes at an angular speed of 90° per second (knee extension flexion; ROM, 90–0°). Isokinetic tests will be performed when patients have no pain or swelling with ROM more than 120° of flexion with full extension. To ensure maximal effort, 3 to 4 training sessions are allowed before performing the test.

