However, so far, almost no studies compared the effects of football and running training interventions on the age-related decline of muscle strength and structure. This is the first study that aims at investigating the differential effects of football and running training response on muscle architecture, patella tendon properties, and thigh muscles. The proposed study should benefit participants’ physical, psychological, and social dimensions. It is assumed that running and football training not only may result in the improvement of the aerobic capacity and systemic arterial blood pressure reductions, but also can improve the functional parameters, including increased explosive power strength, balance, agility, and functional capacity. As our primary hypothesis, we expect moderate differences between both groups in muscle architecture CSA, FL, MT, PA, knee ROM, passive resistive torque, work, power, and tendon length and thickness as football entails are broader and multimodal muscular stimulus compared to aerobic training alone. These may lead to overall decrease in obesity risk and stress, and it could also prevent heart diseases, maintain muscle mass, and reduce the risk of depression. Moreover, the training programs may enhance muscle architecture and tendon thickness that causes a perceptible decrease in the probability of dynapenia and sarcopenia in the future.

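### Read literally, the plan takes knee range of motion at 90°/s with a participant-chosen stop, so each 0.1 s of stop delay adds 9° to the recorded angle; the speed needs to be reconciled and fixed.

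*Protocol article*

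**What the plan says.** Three parts of the protocol article bear on how ROM is obtained.

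- **Outcomes {12}, primary outcome.** A single sentence gives one speed for four quantities: the dynamometer is used "to estimate knee range of motion (ROM), passive resistive torque, power, and work for thigh muscles in an angular speed of 90° per second". ROM stands first in that list, and the section gives no second speed.
- **Range of motion measurement (under {18a}).** No speed appears here. The participant controls the motor and his own sensation ends the movement: "They will then regulate the motor of the dynamometer to get into dorsiflexion (stretching) position until the point of discomfort is reached".
- **Passive resistive torque, and Isokinetic muscular power and work test (under {18a}).** Each restates 90°/s for its own test, and each has a set arc. The torque test runs through "six continuous cycles between 10° plantar flexion and 10° dorsiflexion at 90°/s"; the power and work test uses concentric strokes between 90° and 0°.

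ROM's standing is mixed. The Discussion puts it in the primary hypothesis: "we expect moderate differences between both groups in muscle architecture CSA, FL, MT, PA, knee ROM, passive resistive torque, work, power". The schedule table lists it at baseline and follow-up. It is absent from the Objectives and from the wording of the primary-outcome heading.

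**The concern.** In the torque and power tests the arc is set beforehand, so a fast lever does not decide where the movement ends. In the ROM test the stop angle is itself the result. If the lever really moves at 90°/s until the man reacts, the recorded angle is the angle at which he felt discomfort plus the distance covered while he reacted and the motor stopped.

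Two consequences follow. Variation in that delay between men and between trials is added noise and can hide a true difference. A systematic change in delay between visits, for instance through familiarity, looks like a change in flexibility. The second matters because the statistical methods use paired t tests to measure the effect of each programme separately, and there is no untrained arm to show a shift common to everyone. Participants know their programme and choose the end point, so blinding the outcome assessors does not protect this measurement.

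The ROM procedure also mixes knee and ankle terms. Correcting that would not remove this problem, because the overshoot depends on speed and delay and not on the joint.

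**Working it through.** The plan states no figure for stop delay, delay variation, ROM SD or expected ROM difference, so there is nothing of its own to reproduce. The speed comes from the document; the other inputs are assumptions shown as ranges.

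**Inputs**
- Speed: 90°/s (Outcomes {12}).
- Total stop delay (reaction plus motor): assumed 0.15–0.40 s.
- SD of that delay: assumed 0.03–0.08 s.
- True between-man SD of ROM: assumed 6–10°.

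**1. Mean overshoot = speed × delay**
- 90 × 0.10 = 9° per 0.1 s
- 90 × 0.15 = 13.5°
- 90 × 0.40 = 36°

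This is an offset. The part common to all men and both visits cancels in both the paired and the between-group comparisons, so 13.5–36° does not measure the harm.

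**2. Added error SD = speed × SD of delay**
- 90 × 0.03 = 2.7°
- 90 × 0.05 = 4.5°
- 90 × 0.08 = 7.2°

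**3. Share of total variance = error² / (error² + true SD²)**

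| Case | Error SD | True SD | Share of total variance | Variance ratio |
|---|---|---|---|---|
| Mild | 2.7° | 10° | 7.29/107.29 = 7% | 1.07 |
| Central | 4.5° | 8° | 20.25/84.25 = 24% | 1.32 |
| Severe | 7.2° | 6° | 51.84/87.84 = 59% | 2.44 |

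Delay accounts for more than half the variance only when 90 × (delay SD) exceeds the true SD. With a true SD of 8° that needs a delay SD above 8/90 = 0.089 s, which is outside the assumed range.

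**4. Systematic shift = speed × change in delay**
- A stop 0.05 s later at the post-test: 90 × 0.05 = 4.5°, which enters each within-group paired comparison in full.
- Between groups: 90 × (shift in one arm − shift in the other). Equal shifts give zero.

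**5. Dependence on speed.** Overshoot is proportional to speed. At an illustrative 5°/s the same delays give 5 × 0.15 = 0.75° to 5 × 0.40 = 2°.

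**The case against.** The strongest reply is that 90°/s during the ROM movement is an inference. The ROM procedure does not state it, although the torque and power procedures each restate theirs. In the joint sentence the speed could be read as belonging only to power and work. Having participants regulate the motor may also mean that they slow it as discomfort approaches. This stands as a limit on certainty. It does not remove the point: if each man sets the speed, that disagrees with the literal reading of the outcomes section, and speed may then differ between men and visits.

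A reader might infer that the recorded angle largely reflects reaction time. The documents do not support that. They give no delay or SD, a common delay cancels, and delay variation is about a quarter of total variance in the central case.

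The plan also has partial safeguards: three to four submaximal practice trials before each assessment, and a test-retest check two weeks before the intervention. Practice may reduce the drift but need not remove it. The check uses a Pearson correlation, which is unchanged when every man's second value shifts by the same amount, so it cannot detect a systematic shift.

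Both arms are active and tested alike, so learning common to both cancels in the football-versus-aerobic comparison, which is the main objective. That stands, and it confines the shift argument to the within-group tests unless the delay changes differently by arm. The sample size rests on vastus medialis pennation angle, so the extra ROM noise does not alter the planned 60 men.

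**Conclusion.** The point holds in a limited form. Taken literally, the plan applies 90°/s to a test whose result is a self-chosen stop angle. That makes ROM sensitive to stop delay at 9° per 0.1 s.

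On the assumptions shown, variable delay adds 2.7–7.2° of error SD, which is 7% to 59% of total variance and about 24% centrally. A 0.05 s systematic shift adds a spurious 4.5° to the within-group results. Bias between groups requires the shift to differ by arm, and the documents give no evidence that it would.

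Only the speed comes from the protocol; the delays and SDs are assumed. Confidence is moderate because the speed is tied to ROM by one joint sentence. On the alternative reading, where each man sets the motor speed, the two sections conflict and still have to be reconciled.

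**What to change.** Reconcile the outcomes section with the ROM procedure:

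- In Outcomes {12}, restrict 90°/s to the tests whose own procedures state it: passive resistive torque, and isokinetic power and work.
- In Range of motion measurement, state one slow constant speed, the same for all men and both visits.
- Record the angle at the moment of the stop signal, not where the lever comes to rest.

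The 5°/s used above only shows how overshoot scales with speed. Averaging repeats (three, say) would reduce trial-to-trial noise, but that number too is only an illustration.

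The cost is a dynamometer setting, a sentence in each of two sections, and slightly longer tests: a 90° arc takes 90/5 = 18 s at 5°/s against 1 s at 90°/s. No extra men, staff or equipment are needed. If baseline ROM has already been taken, changing the speed for the post-test alone would break the pairing. In that case keep the baseline setting, state what it was, and treat within-group ROM changes with caution.

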#### Passive resistive torque

Participants will be positioned with their hips at approximately 80° (to minimize hamstring stiffness) and their knees at a maximal extension. Stabilization straps are placed over the knee, foot, and ankle. The knee moves passively through six continuous cycles between 10° plantar flexion and 10° dorsiflexion at 90°/s, with neutral (0°) being the line of the tibia perpendicular to the footplate. The participants will be instructed to do the maximum plantar and dorsiflexion. Visual analysis of the curves will demonstrate consistent torque profiles, which indicate passive resistive torque.

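### The knee ROM and passive-torque procedures describe an ankle test, and muscle power and work are defined as peak torque

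*Protocol article*

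**What the plan says.** Outcomes {12} of the protocol article opens with the heading "Primary outcome: muscle architecture, tendon length, tendon thickness, muscle power, torque, and work". In the text below it, the isokinetic dynamometer "will be used to estimate knee range of motion (ROM), passive resistive torque, power, and work for thigh muscles in an angular speed of 90°" (that is, 90°/s). The primary hypothesis in the Discussion again lists knee ROM, passive resistive torque, work and power.

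The procedures follow under {18a}:

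- **Range of motion measurement.** The foot is strapped to a footplate, and "the upper leg will be fixed with a strap to avoid any movement of the knee". The movement is into dorsiflexion, up to discomfort.
- **Passive resistive torque.** The knees are at maximal extension, with straps over knee, foot and ankle. Then "The knee moves passively through six continuous cycles between 10° plantar flexion and 10° dorsiflexion at 90°/s", with zero where the tibia is at right angles to the footplate. The next sentence reads "The participants will be instructed to do the maximum plantar and dorsiflexion". The readout is a visual inspection of the curves.
- **Isokinetic muscular power and work test.** Seated, over a knee range of 90–0°, "patients perform 4 maximal concentric strokes at an angular speed of 90° per second".

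The outcomes section defines the active variables differently: "Knee extensor and flexor muscle power and work will be measured as the peak torque obtained over 3 trials", in a mode called both passive and concentric. For the passive variable it says "Passive resistive torque will be obtained over 3 repetitions at the same speed degree".

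**The concern.** Plantar flexion and dorsiflexion are movements of the ankle, and the angle between tibia and footplate is an ankle angle. A test built on them cannot give knee ROM or the passive resistance of the thigh muscles. Passive torque also presupposes a relaxed participant. Maximal voluntary effort adds an unknown active component that may change with training, and may change differently in the two arms.

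Power and work are different quantities from torque. If both are recorded as peak torque, a difference between the football and aerobic groups in one outcome reappears under two further names. A reader could take that for three concordant findings.

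No analysis can repair either fault afterwards if the wrong joint was tested or the wrong quantity recorded.

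**Working it through.** No sample size, alpha or power figure enters this point. The check sets the outcome definitions beside the procedures, with short arithmetic on the device settings.

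**1. Joint tested**

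| Feature | ROM procedure | Passive-torque procedure | Isokinetic test |
|---|---|---|---|
| Outcome named | Knee ROM | Passive torque, thigh muscles | Knee extensor and flexor power |
| Fixation | Foot on footplate; upper leg strapped against knee movement | Straps over knee, foot, ankle | Not stated |
| Movement | Dorsiflexion | Plantar flexion to dorsiflexion | Knee extension–flexion |
| Zero or start | Knee fully extended, then a neutral knee position of 90° | Tibia perpendicular to footplate | Knee range 90–0° |
| Joint implied | Ankle, with a contradictory knee start position | Ankle | Knee |

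In the passive-torque column, fixation, movement and zero reference all point to the ankle. Only the word knee points elsewhere, so this is more than one mistyped term. The arc agrees: 10° + 10° = 20°, against 90° in the isokinetic test. The ROM column is less uniform. Its movement and footplate are those of an ankle test, but the knee is first fully extended and then placed at 90°, and both cannot describe one starting position.

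**2. Passive or active.** The passive-torque section says that the joint is moved passively and then asks for maximal plantar and dorsiflexion. Both cannot hold during the same recording. Visual inspection of curves also fixes no number to enter a *t* test.

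**3. Power and work.** With torque T at joint angle θ:

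- work per stroke: W = ∫ T dθ
- average power: W / t, where t is the stroke time
- peak torque: max T

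Two participants with the same max T but differently shaped curves do different work, so work cannot be read from peak torque. Under the outcomes-section definition, torque, power and work are one number per muscle group. For two groups (extensors, flexors) that is 3 × 2 = 6 labels and 2 distinct values.

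The isokinetic test could supply all three. A full stroke lasts 90° ÷ 90°/s = 1 s, so at constant speed average power in watts equals work in joules: W / 1 s. Peak instantaneous power would be max T × (90 × π/180) = max T × 1.57 rad/s. Even when properly defined, power at this single speed will therefore closely follow work (if average) or peak torque (if peak). Work is the quantity that the present definition loses outright.

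**4. Counts**

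| Test | Outcomes {12} | Procedures {18a} |
|---|---|---|
| Passive torque | 3 repetitions | 6 cycles |
| Isokinetic test | 3 trials | 4 strokes |

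**The case against.** Several points on the other side have force.

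- *The isokinetic section describes a proper active knee test.* This stands. A reader might infer that the main objective on thigh power, work and torque cannot be answered. The documents do not support that: peak torque is validly obtained, and the same test can yield work and power once they are defined.
- *Fixing the upper leg is normal in a knee test, and moving to 90° implies knee movement.* This stands in part. The ROM section contradicts itself, so it would be too strong to say that it certainly yields no knee information. But the strap's stated purpose is to stop the knee moving, and the movement named is dorsiflexion.
- *Knee ROM and passive torque may not be primary.* Neither is named in the primary-outcome heading, which lists only torque, or in Objectives {7}. The schedule (Table 4) lists ROM but not passive torque. Yet both stand in the text under that heading and in the primary hypothesis. Their status is unclear, but they are not incidental.
- *The counts may separate what is performed from what is analysed.* Possible, since the article does not say. They are secondary ambiguities.
- *At fixed speed, peak power is proportional to peak torque.* True, but the article does not say peak power, and the argument does not extend to work.
- *Staff may run a sound knee test regardless.* Then the published procedure does not describe the trial.

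A reader might also put a large share of all primary variables in doubt. The article gives no count of primary variables to support such a fraction. The ultrasound outcomes, including the vastus medialis pennation angle on which Sample size {14} rests, are untouched.

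**Conclusion.** The point holds in two parts of different weight.

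First, knee ROM and passive resistive torque would not validly measure the knee if the procedures are followed as written. The case is clearest for passive torque, where everything but the joint's name describes the ankle and the effort instruction contradicts the test. For ROM the text is contradictory as well as misdirected.

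Second, power and work are misdefined. Both duplicate peak torque for each muscle group. This is a fault of definition only, because the knee test that could supply them is already in the protocol.

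The conclusion assumes that the published text is the procedure used. The article does not show what was done in the laboratory. The correction is essential because no later adjustment turns ankle readings into knee data.

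**What to change.** Reconcile the primary-outcome text in {12} with the three dynamometer sections in {18a}:

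1. Describe ROM and passive torque as knee flexion–extension: thigh fixed, lower leg moving, participant told to relax, one starting position, one angle range and one cycle count.
2. Give passive torque a numeric readout, such as the torque at a stated angle or the mean over a stated arc, in place of visual inspection.
3. Define peak torque (N·m), work (J) and power (W) as separate outputs of the active concentric knee test, with one repetition count. Say whether power is average or peak, remove the passive label, and say how many repetitions are performed and how many analysed.
4. State whether knee ROM and passive torque are primary, and make the heading, objectives, hypothesis and schedule agree.

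Before any testing this would cost only rewritten text, on the same device with no added visits. The stated dates suggest that time has passed: dynamometer baseline tests were due by 16 March 2020, training was to end on 15 July 2020, and the article appeared on 9 December 2020. If the tests are done, the authors should state what was actually performed. Work and power can then be derived if the torque curves were stored, which the article does not say. If the ankle set-up was used, the baseline knee values cannot be recovered: relabel those two outcomes as ankle measurements, disclose any voluntary effort, and draw no knee conclusions from them.

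### The passive resistive torque test also instructs a maximal movement; if that applies during the cycles, the recorded torque is passive plus voluntary and cannot be read as a passive property.

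*Protocol article*

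**What the plan says.** Under Plans for assessment and collection of outcomes {18a}, the section Passive resistive torque describes three steps in sequence.

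- The movement: "The knee moves passively through six continuous cycles between 10° plantar flexion and 10° dorsiflexion at 90°/s".
- The instruction to the men: "The participants will be instructed to do the maximum plantar and dorsiflexion".
- The reading of the record: "Visual analysis of the curves will demonstrate consistent torque profiles, which indicate passive resistive torque".

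Under Outcomes {12}, the relevant heading is "Primary outcome: muscle architecture, tendon length, tendon thickness, muscle power, torque, and work". The text below it says that the dynamometer "will be used to estimate knee range of motion (ROM), passive resistive torque, power, and work for thigh muscles", and then gives a count: "Passive resistive torque will be obtained over 3 repetitions at the same speed degree". The primary hypothesis in the Discussion includes "knee ROM, passive resistive torque, work, power, and tendon length and thickness" among its items.

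Maximal voluntary effort has its own section, Isokinetic muscular power and work test, where "patients perform 4 maximal concentric strokes at an angular speed of 90° per second". A range whose end point the participant sets himself also has its own section, Range of motion measurement.

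**The concern.** Passive resistive torque is the resistance that a limb offers while its owner is inactive and a device moves it. A voluntary contraction during the movement adds muscle torque to the reading. The protocol describes passive movement, then directs a maximal one, then treats the curves as passive torque.

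The contamination would not be harmless noise. Voluntary torque depends on strength and motivation, and twelve weeks of training may change both, perhaps differently in the two arms. Under Who will be blinded {17a}, participants know their allocation. Blinded assessors do not help when the signal itself depends on the participant's effort. The planned paired and independent t tests could then show a change in strength or effort that is reported as a change in passive tissue properties.

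**Working it through.** The protocol states no torque figure, so there is nothing to reproduce. The check compares the passages and adds two short pieces of arithmetic.

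**1. Can the instruction mean something compatible with passive movement?**

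- *Move to your maximum range.* The preceding sentence fixes the arc at 10° each way, so the sweep is 10° + 10° = 20°. At 90° per second and constant speed, one sweep takes 20 / 90 = 0.22 s. The device sets the end points, and there is no room for a limit chosen by the participant.
- *It belongs to the range test.* That test has its own section, in which the participant controls the motor up to the point of discomfort.
- *It belongs to the strength test.* That test also has its own section, with 4 maximal strokes.

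None of these readings fits the sentence where it stands, between the cycles and the interpretation of their curves. Its natural meaning there is that it applies to the cycles, although the text does not say so explicitly.

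**2. What would be recorded?** Let P be passive torque and A the voluntary torque during the sweep, signed so that effort against the motion is positive. The recorded value is R = P + A. For a before/after change or a difference between arms, ΔR = ΔP + ΔA. If passive properties do not change, ΔP = 0 and ΔR = ΔA, so the whole observed difference is effort or strength. Effort in the direction of motion makes A negative and lowers the reading. The direction of the error is therefore not fixed.

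**3. Would consistent curves reveal it?** Agreement between cycles shows that R is repeatable. If a man makes a similar effort on each cycle, A is repeatable too, and the curves agree with A present. Consistency does not separate P from P + A.

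**4. Repetition count.** Outcomes {12} gives 3 repetitions; the procedure gives six continuous cycles. At 2 × 20° = 40° per cycle, six cycles take 6 × 40 / 90 = 2.7 s and three take 1.3 s. The article does not say whether the 3 are a subset of the six.

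**5. Joint.** The procedure says that the knee moves, but describes the movement as plantar flexion and dorsiflexion, with neutral defined by the tibia and a footplate. Outcomes {12} assigns the measure to the thigh muscles. This is a further inconsistency in the same paragraph. A maximal effort would spoil a passive measure at either joint.

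**The case against.** The best defence is that this is one badly worded sentence. It does not say when the instruction applies, and assessors who know the test may well ask men to relax. A reader might infer that the test certainly records voluntary torque in place of passive torque, in every man at both visits. The document does not support that: the timing is inferred from position, actual practice is unknown, and even under full compliance the record would be the sum of the two torques. The conclusion must stay conditional.

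A reader might also treat the sentence about consistent profiles as a faulty acceptance rule. It states an expectation; no rule for accepting or rejecting trials is given. A condensed article may leave such a rule, or a cue to relax, to the full protocol, so their absence is not the point. What stands is that the one instruction the article does give contradicts the passive movement it describes.

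It is tempting to express the error as a multiple of the true value. Any multiple would rest wholly on assumed torques for a joint that the text does not clearly identify, so none is given.

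Finally, the measure is one of many. The primary heading says only torque, Table 4 does not list torque, and the sample size rests on the pennation angle of vastus medialis. This limits the reach of the problem but does not remove it, because passive resistive torque appears in the primary outcome text and in the primary hypothesis.

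**Conclusion.** The contradiction is real and nothing else in the article resolves it. If the maximal instruction is applied during the cycles, the values are passive plus voluntary torque, and neither a before/after nor a between-arm difference can be interpreted as a change in passive properties. The count of 3 against six is a separate, definite disagreement.

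This rests on two assumptions: that the instruction applies where it is placed, and that men follow it at least in part. The size and direction of the error cannot be derived from the document. One measure within the primary group is affected; the ultrasound outcomes and the sample size calculation are not. The point should be corrected, but it does not threaten the trial as a whole.

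**What to change.** - Remove the maximal-movement instruction from the passive test, or move it to the test it belongs to.
- State that participants stay relaxed while the device moves the limb.
- Exclude cycles with evident voluntary effort.
- Reconcile Outcomes {12} and the procedure to one cycle count, and say which cycles enter the analysis.
- Reconcile the knee and ankle wording in the same paragraph. Correcting the instruction alone would not make the described set-up a clear measure of the thigh muscles.

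Before testing, this costs a few sentences and no equipment, visits or participants. By the article's own dates, however, baseline dynamometry was to finish by 16 March 2020 and training on 15 July 2020, with post-tests the following week, while publication was on 9 December 2020. If those dates held, new wording cannot repair the data. The results paper should then state which instruction was given and how many cycles were used. If the instruction was maximal, it should not interpret the values as passive torque.
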